**Methods:**

This study is a randomized controlled trial. Women undergoing primary treatment (during or after chemotherapy) for breast cancer (stages I–III) will be randomly assigned to MTHE (twice a week) or HE (once a week). MTHE components are mobility, aerobic, balance, resistance, and flexibility home-based exercises, supervised by video call. The primary study outcome is cancer-related fatigue. The secondary outcomes are quality of life, symptoms of depression and anxiety, physical activity level, cancer-related cognitive impairment, and functional capacity. Other outcomes are adherence to interventions and a follow-up questionnaire evaluating the individual perception in motivation, lifestyle changes, and main barriers to participation. All outcomes will be remotely assessed before and after intervention. Our analysis will follow the intention-to-treat approach and per-protocol criteria, with additional sub-group analysis.

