### Primary outcome

The primary study outcome is cancer-related fatigue, which will be assessed using the Piper fatigue scale. Cancer-related fatigue was chosen as the primary outcome because it is a widespread side effect caused by chemotherapy, and it is identified among high-priority cancer- and treatment-related toxicities based on its potential to affect cancer care rapidly [28, 38].

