#### Sample size

The sample size estimation was based on the number of patients feasible to collect given our financial resources during the period of the study (concomitant with the COVID-19 pandemic )[29]. We estimate that the total sample will be around 30 participants. Therefore, approximately 15 women will be enrolled in each group.

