#### Statistical considerations

Generalized Estimating Equations (GEE) and Bonferroni post hoc tests will be used for comparison between time points (baseline and post-intervention) and groups (MTHE and HE) for both per-protocol and intention-to-treat analyses. The per-protocol analysis (PP) will count all women with training frequency ≥ 70% of intervention sessions (≥ 16 sessions for participants allocated in the exercise program, and ≥ 8 sessions for participants allocated to the education program). For the intention-to-treat analyses, the incomplete data (i.e., missing values) will be estimated using maximum likelihood estimation by the automatic regression imputation method.

Additionally, we plan to carry out subgroup analysis stratifying both groups by clinical characteristics of the tumor (histological type of tumor, tumor staging, and status of hormone receptors) and treatment (chemotherapy and radiotherapy protocols). Considering that withdrawals may occur due to specific harms or other non-anticipated reasons, we will assess whether additional grouping (indicator) should be made due to different missing data patterns. Therefore, we will qualitatively document reasons and details of withdrawals on a case-by-case basis. Continuous variables will be summarized according to intervention groups at baseline, if applicable, and end of trial using arithmetic or geometric means, standard deviations, ranges, and interquartile ranges as appropriate. According to intervention groups, categorical variables at baseline and end of the trial (if applicable) will be summarized as absolute number and proportion of subjects (%). Standardized effect sizes will be calculated by dividing the between-group difference of the post-intervention means by the pooled baseline standard deviation. The significance level established for all analyses will be *p* < 0.05, and all statistical procedures will be analyzed and processed using the SPSS version 22.0 software.

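### The effect size ignores baseline fatigue and the GEE treats it as an outcome; one baseline-adjusted contrast would be more precise and would keep estimate and test in step

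*Protocol article*

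**What the plan says.** Under Primary outcome: "The primary study outcome is cancer-related fatigue, which will be assessed using the Piper fatigue scale". The abstract says of timing: "All outcomes will be remotely assessed before and after intervention". The article also places baseline assessment before randomization, so every randomized woman should have a pre-allocation Piper score.

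Statistical considerations fixes two things about how that score is used.

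- Effect size: "Standardized effect sizes will be calculated by dividing the between-group difference of the post-intervention means by the pooled baseline standard deviation".
- Testing: GEE, together with "Bonferroni post hoc tests will be used for comparison between time points (baseline and post-intervention) and groups". Baseline is thus one of the two levels of time in the model. It is not named as a covariate.

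Sample size is set by feasibility: "We estimate that the total sample will be around 30 participants", so that "approximately 15 women will be enrolled in each group". Allocation is 1:1 in blocks of random size, with no stratification described. The threshold is 0.05, and sidedness is not stated.

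**The concern.** The trial asks one between-arm question: is fatigue lower after exercise plus education than after education alone? In a small randomized trial, each woman's own starting score is usually the best available predictor of her final score. The effect-size formula makes no use of it in the numerator. Any chance difference between arms at baseline therefore passes in part into the published effect.

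The GEE does contain the baseline scores, but as a response. If its group-by-time term is the test, the quantity tested is a difference in change, while the effect size is a difference in final means. The two differ by exactly the observed baseline imbalance. The article could then report an effect size and a p-value that answer different questions and point to different strengths of evidence. Precision is also lost, and with about 30 women there is little to spare.

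**Working it through.** **Inputs from the article.** n = 15 per arm (2 × 15 = 30, the stated total) and alpha 0.05. There is no power calculation to reproduce.

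**Assumptions.** Two-sided test, equal SDs, no dropout, and a baseline-to-post correlation r of 0.5 to 0.7. The article gives no r. All effects are in baseline-SD units.

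**Step 1: chance imbalance.** The SD of the baseline difference is sqrt(2/15) = 0.365. P(|difference| > 0.5 SD) = 2 × (1 − Φ(0.5/0.365)) = 2 × (1 − Φ(1.37)) = 0.17.

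**Step 2: what a 0.5 SD imbalance does.** Given a baseline difference D, the post-only difference is shifted by r × D and the change difference by −(1 − r) × D.

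- r = 0.5: post-only +0.25, change −0.25.
- r = 0.7: post-only +0.35, change −0.15.

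In each case the gap is 0.5 SD, the imbalance itself. If the exercise arm starts 0.5 SD more fatigued, the post-only effect size understates its benefit and the change contrast overstates it.

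**Step 3: precision.** The variance factors relative to post-only are 1 (post-only), 2(1 − r) (change, which is the saturated group-by-time contrast) and 1 − r² (ANCOVA). The detectable effect is for 80% power from the noncentral t distribution (28 degrees of freedom; 27 for ANCOVA).

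| r | Variance factor: change | Variance factor: ANCOVA | Detectable: post-only | Detectable: change | Detectable: ANCOVA |
|---|---|---|---|---|---|
| 0.5 | 1.00 | 0.75 | 1.06 | 1.06 | 0.92 |
| 0.6 | 0.80 | 0.64 | 1.06 | 0.95 | 0.85 |
| 0.7 | 0.60 | 0.51 | 1.06 | 0.82 | 0.76 |

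ANCOVA removes r² of the post-only variance: 25% at r = 0.5 and 49% at r = 0.7. That equals post-only analysis of 30/0.75 = 40 or 30/0.51 = 59 women. Since 2(1 − r) − (1 − r²) = (1 − r)², change is always less precise than ANCOVA when r is below 1.

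At a weaker r = 0.3 the variance saving is only 9%. The detectable effects are then 1.06 × sqrt(1.4) = 1.25 SD for change and 1.06 × sqrt(0.91) = 1.01 SD for ANCOVA.

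**Step 4: bias.** In 10,000 simulated trials per r (0.3, 0.5, 0.7) with a true effect of 0.80 SD, all three estimators averaged 0.80 to two decimals.

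**Step 5: Bonferroni, conditionally.** Suppose a post hoc post-intervention pair decided the hypothesis. With two comparisons (alpha 0.025) the detectable effect is 1.18 SD, and power at 1.06 SD falls from 80% to 70%. With all six pairs of the four group-by-time means (alpha 0.05/6) it is 1.36 SD, and power falls to 53%. The article states no number of comparisons.

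**The case against.** The strongest reply is that the GEE already uses baseline. Post hoc tests follow a model, and in a two-group, two-time model the natural between-arm test is group-by-time, which is a difference in change. That stands. A reader might infer that the hypothesis tests ignore baseline fatigue altogether, but the text does not support this. It supports only that baseline is not conditioned on. If group-by-time decides, the fair comparison is change against ANCOVA. The gain is then modest at r = 0.7 (0.82 against 0.76 SD) and larger at r = 0.5 (1.06 against 0.92 SD).

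A reader might also infer that power is certainly lost a second time through Bonferroni. The article does not say that a post hoc pair decides the hypothesis, and a correction on such pairs leaves the group-by-time test untouched. The figures in Step 5 are therefore conditional.

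An unadjusted comparison in a randomized trial is valid. The harm is lost precision and error conditional on the imbalance in this one trial. It is not bias.

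Finally, an analysis plan that is not shown may name the deciding contrast and the covariates, so their absence from the article is not held against it. What remains is what the article does fix: the effect-size formula and the role of baseline as a time point.

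The mix of "Women undergoing primary treatment (during or after chemotherapy) for breast cancer" is a side issue. Subgroup analyses by treatment protocol are planned. These do not adjust the main comparison, but the phase mix is not ignored either.

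**Conclusion.** The point holds as one of efficiency and consistency, not of validity. The effect size as defined carries chance baseline imbalance into the result. An imbalance above 0.5 SD has a 17% probability, and one of 0.5 SD shifts the effect size by 0.25 to 0.35 SD. A group-by-time test would shift the other way, by 0.25 to 0.15 SD, so the published effect and its test may not agree. Whichever of the two contrasts decides, baseline adjustment is more precise: 0.92 to 0.76 SD detectable, against 1.06 SD post-only and 1.06 to 0.82 SD for change.

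The 17% follows from 15 per arm alone, under a normal approximation. The other figures rest on the assumed r of 0.5 to 0.7, equal SDs, no dropout and two-sided 0.05. A lower r shrinks the gain over post-only and enlarges the gain over change. No definite Bonferroni loss is established.

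**What to change.** State one primary test: the between-group difference in post-intervention Piper total, adjusted for baseline Piper total, by ANCOVA or a repeated-measures model that constrains the baseline means to be equal. Test it at two-sided 0.05 with no pairwise Bonferroni correction. Compute the standardized effect size from that same adjusted difference, still divided by the pooled baseline SD. Report within-arm changes descriptively, and use the same model for each secondary scale with its own baseline.

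The cost is analysis wording and one degree of freedom, since the baseline scores are already collected. Adding treatment phase (during or after chemotherapy) as a covariate is optional and would cost one more.

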#### Assignment of interventions and blinding

After consent, each participant will receive an internal identifier number. After completing the baseline assessments, participants are randomized to either the MTHE or HE. A blinded investigator created a computer-generated randomization sequence, via random function (Excel software), 1:1 ratio, with a block of random sizes that are not disclosed to ensure concealment. The allocation concealment is implemented by researchers in charge of requesting randomization for one of the blind investigators with access to the randomization list ([name], [name]), via email, from the identifier number. A researcher ([name]) allocates individuals in the groups by phone call or WhatsApp message. Randomization requests follow the order in which participants complete the baseline assessments. The allocation date of the participants is recorded in an Excel spreadsheet.

Blinding will be applied for assessors of all primary and secondary outcomes, except physical activity level and cognitive function (the researcher monitoring these two evaluations is not blinded, but both questionnaires are self-administered). Participants are asked to omit their assigned group and not talk about their interventions during the outcome assessments. Due to the nature of the intervention, the study staff supervising training sessions and participants are non-blinding. In unblinding cases, the principal investigator will be notified with the participant ID, date, and reasons for unblinding.

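### The planned effect size ignores baseline fatigue in its numerator, so with about 15 women per arm it is noisier than the collected data allow

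*Protocol article*

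**What the plan says.** Statistical considerations defines the effect measure in one sentence: "Standardized effect sizes will be calculated by dividing the between-group difference of the post-intervention means by the pooled baseline standard deviation". The same section plans generalized estimating equations (GEE) with Bonferroni post hoc tests for "comparison between time points (baseline and post-intervention) and groups (MTHE and HE) for both per-protocol and intention-to-treat analyses". In that model baseline is one of the compared time points, so it is a response and not a covariate. The article names neither a baseline-adjusted difference nor the contrast that will carry the between-group conclusion.

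Sample size states that "approximately 15 women will be enrolled in each group" and gives resources as the basis: "The sample size estimation was based on the number of patients feasible to collect given our financial resources during the period of the study". Assignment of interventions and blinding describes allocation as "1:1 ratio, with a block of random sizes that are not disclosed to ensure concealment" and mentions no stratification by fatigue. According to that section and Table 2, baseline fatigue is measured before allocation.

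**The concern.** Blocked 1:1 allocation balances the numbers of women, not their fatigue scores. In a trial this small, the arms can easily start some distance apart. Women who are more fatigued at baseline tend to be more fatigued at 12 weeks, so part of any starting gap reappears in the post-intervention difference and is reported as effect. Dividing by the baseline SD rescales that gap but does not remove it.

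The sample size rests on feasibility, with no target difference or power stated, so readers will look to the estimated effect at least as much as to the p-value. Precision in that estimate is worth having, and the plan leaves some unused although the baseline scores are in hand. The type I error of the test is not at issue.

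**Working it through.** **The plan's own figure.** 2 × 15 = 30 agrees with the stated total of around 30. There is no power calculation to reproduce.

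**Inputs.** n = 15 per arm (Sample size); effect-size formula (Statistical considerations). The baseline-to-post correlation rho is not in the article and is assumed to lie between 0.3 and 0.8. Everything is in SD units, with equal SDs at both times and complete data.

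**Step 1, chance imbalance at baseline.**
- SE = sqrt(2/n) = sqrt(2/15) = 0.365; 95% range ±1.96 × 0.365 = ±0.72 SD.
- P(imbalance above 0.3 SD in either direction) = 2 × (1 − Φ(0.3/0.365)) = 41%.
- P(above 0.5 SD) = 2 × (1 − Φ(0.5/0.365)) = 17%.

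**Step 2, carry-over.** Expected shift in the post-intervention difference = rho × imbalance. For an imbalance of 0.5 SD:

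| rho | 0.3 | 0.5 | 0.7 | 0.8 |
|---|---|---|---|---|
| shift (SD) | 0.15 | 0.25 | 0.35 | 0.40 |

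**Step 3, standard errors of three estimators of the same effect.**
- Post-intervention only (as planned): sqrt(2/n) = 0.365 at any rho.
- Difference in change: sqrt(2/n) × sqrt(2(1 − rho)).
- Baseline-adjusted: sqrt(2/n) × sqrt(1 − rho²), times sqrt(1 + 1/(2n − 4)) = sqrt(27/26) = 1.019 because the slope is estimated from 30 women.

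| rho | planned | change | adjusted, slope known | adjusted, slope estimated |
|---|---|---|---|---|
| 0.3 | 0.365 | 0.432 | 0.348 | 0.355 |
| 0.5 | 0.365 | 0.365 | 0.316 | 0.322 |
| 0.7 | 0.365 | 0.283 | 0.261 | 0.266 |

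Simulation of 100,000 trials per setting (bivariate normal) agrees with the last column. The variance ratio of adjusted to planned, (1 − rho²) × 27/26, is 0.945, 0.779 and 0.530, a saving of about 5%, 22% and 47%.

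**Step 4, can the effect size and the test disagree?** If the test is the group-by-time contrast, it estimates the difference in change. With no true effect, the planned effect size and the difference in change have opposite signs in 30%, 33% and 37% of trials (rho 0.3, 0.5, 0.7), and with a true effect of 0.3 SD in 22% to 23%. Most of these are pairs of small, non-significant estimates. Requiring the contrast to be significant (t-test on change, p < 0.05) as well as opposite in sign leaves:

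| true effect | rho 0.3 | rho 0.5 | rho 0.7 |
|---|---|---|---|
| 0 | 0.3% | 0.5% | 0.9% |
| 0.3 SD | 0.2% | 0.4% | 1.3% |
| 0.5 SD | 0.1% | 0.4% | 1.4% |

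The frequency rises with rho, but stayed below 3% at rho 0.8 in the same simulation.

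**The case against.** A reader might infer that the planned measure is biased, or that it estimates something other than what the test addresses. The article does not support that. Under randomisation the post-intervention difference, the difference in change and the baseline-adjusted difference all have the treatment effect as their expectation. The planned measure is off by a foreseeable amount only conditional on an imbalance that has actually occurred.

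A reader might also infer that the effect size and the p-value beside it will often contradict each other. Step 4 shows that a significant contrast with an opposite-signed effect size is rare. The article, moreover, does not name the group-by-time contrast as the reported test. If the Bonferroni comparison of the arms at post-intervention is meant, it tests exactly the numerator of the effect size and the two agree. Both would then carry the same baseline imbalance. Taking marginal means from the GEE would not remove it: with group, time and their interaction and complete data, these equal the observed means.

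Two further objections stand. The gain is small if rho is low (about 5% of the variance at 0.3). And the planned baseline and end-of-trial summaries by arm, with participant-level data available on request, let others see an imbalance and re-analyse. Neither is a reason to publish the less precise figure when baseline is already measured.

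The article mentions no confidence interval or small-sample correction for the effect size. A condensed article may leave these out, and the correction is small: 1 − 3/(4 × 28 − 1) = 0.973, or 2.7%.

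**Conclusion.** The point holds as one of avoidable imprecision in the reported magnitude. It is not a point about bias or an invalid test. At 15 per arm the planned effect size has a standard error of 0.365 SD; baseline adjustment would bring it to about 0.35, 0.32 or 0.27 at rho 0.3, 0.5 or 0.7. Given a 0.5 SD imbalance, which chance produces or exceeds in 17% of trials, the planned figure would be displaced by an expected 0.15 to 0.40 SD over rho 0.3 to 0.8.

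The 0.365 and the 17% follow from the stated sample size under a normal approximation. The carry-over and the gain depend on rho, which the article does not give, and on equal SDs and complete data. The definition is explicit in the article, so an analysis plan that followed it would inherit the weakness.

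**What to change.** Redefine the standardized effect size as the baseline-adjusted between-group difference at post-intervention, divided by the pooled baseline SD. Keep that divisor.

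Changing this sentence alone is not enough, because the GEE as described treats baseline as a response and yields no adjusted difference. State also that the between-group model does one of the following:

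- includes the baseline score as a covariate, with the post-intervention score as the response; or
- keeps both time points but constrains the arms to a common baseline mean. The working correlation must then not be independence, since under independence the constrained model returns the unadjusted post-intervention difference.

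Name the resulting group contrast as the source of both the p-value and the effect size.

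Do not move to a change-score effect size instead: at rho 0.3 its standard error is 0.432, against 0.365 for the planned measure.

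The cost is a small change to the model specification, best made before outcome data by arm are examined. No new data, visits or participants are needed.

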**Discussion:**

To our knowledge, this is the first randomized clinical trial in breast cancer patients using a face-to-face videoconference strategy to supervise physical exercise. Our hypothesis is of superiority for the effects of MTHE on primary and secondary outcomes compared to the effects of only the health education intervention.

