As an alternative methodology, telehealth is an important tool to improve the monitoring and delivering of a physical exercise program for cancer patients, besides being safe and low-cost [5, 48]. Telehealth can be defined as distance-based interventions delivered using information and communication technologies to assess, educate, monitor, and/or guide physical exercises or other health care interventions [5, 45]. However, the efficacy of home-based exercise on fatigue and psychosocial outcomes in breast cancer patients undergoing primary treatment is not entirely established. A meta-analysis including seven unsupervised home-based interventions [55] found no positive effect on cancer-related fatigue in patients ongoing breast cancer treatment. On the other side, a recent meta-analysis study including cancer survivors demonstrated that home-based physical activity interventions induced small improvements in fatigue for up to 9 months [23]. It is important to highlight that the participation rate in these home-based interventions was higher (mean 55.33%) than in previous studies during (41–43% )[11, 54] and after (37%) [26] treatment. Although adherence to exercise is a positive feature in home-based interventions, the heterogeneity among exercise protocols is remarkable regardless of the environment [59]. Previous interventions did not attend principles of training and exercise recommendations as an indication of the quantity and multiples components (i.e., mobility, aerobic, balance, resistance, and flexibility exercises). Also, these studies failed to adequately report exercise prescription variables (i.e., frequency, intensity, time, and type), hindering the protocol application by health professionals and the comparison between studies [15, 39].

Therefore, our study aims to evaluate the effect of telehealth multicomponent training plus a health education program, compared to a health education only, on fatigue, quality of life, anxiety and depression symptoms, and functional capacity in women undergoing primary treatment for breast cancer. The choice of the active comparator group intends to reach the principle of equipoise and partially accounts for research participation effects (Hawthorne effect). Our central hypothesis is of superiority for the effects of multicomponent training plus a health education program group (MTHE) on primary and secondary outcomes compared to the effects of only a health education program (HE).

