#### Assessment of primary outcome

##### Cancer-related fatigue

Cancer-related fatigue is determined through an interview by scores from the Piper Fatigue Scale, the Portuguese-validated version [35, 41]. Piper Fatigue Scale consists of 22 items, ranging from 0 (no fatigue) to 10 (severe fatigue), to assess four dimensions of subjective fatigue and total fatigue. Six items will evaluate behavioral fatigue (i.e., impact of fatigue on school or work, interacting with friends, and the overall interference with enjoyable activities). The affective fatigue includes five items that assess the emotional meaning attributed to fatigue. Other five items comprise the sensory fatigue (i.e., mental, physical, and emotional fatigue symptoms). The cognitive/mood fatigue includes six items to assess the impact of fatigue on concentration, memory, and the ability to think clearly. Total fatigue is measured by averaging these four dimensions.

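### Superiority is hypothesised on primary and secondary outcomes, every analysis in two sets is tested at 0.05, and no single score or set is named as deciding

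*Protocol article*

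**What the plan says.** Four statements in the Protocol article have to be read together.

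- **Scope of the claim.** The Discussion part of the Abstract states: "Our hypothesis is of superiority for the effects of MTHE on primary and secondary outcomes". The end of the Background repeats this as the central hypothesis.
- **Primary outcome.** Under Primary outcome: "The primary study outcome is cancer-related fatigue, which will be assessed using the Piper fatigue scale". Under Cancer-related fatigue, the scale is said "to assess four dimensions of subjective fatigue and total fatigue". The total is defined there as the average of the four dimensions, but it is not declared to be the primary score.
- **Analysis sets.** The Methods part of the Abstract says "Our analysis will follow the intention-to-treat approach and per-protocol criteria". Statistical considerations applies the same model "for both per-protocol and intention-to-treat analyses". Neither place says which set decides.
- **Error level.** Statistical considerations: "The significance level established for all analyses will be" p < 0.05. The only adjustment is in the sentence "Generalized Estimating Equations (GEE) and Bonferroni post hoc tests will be used for comparison between time points" and groups. It concerns contrasts within one outcome, not several outcomes, scores or sets.

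**The concern.** Each statement is ordinary by itself. Together they let a significant result on any of five fatigue scores, or on any secondary scale, in either set, count as support for the stated hypothesis. A 5% level per test does not give a 5% risk for a claim that can be met in so many ways.

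The stakes are higher because the trial is small: the Sample size section gives about 30 women, a number set by feasibility. With about 15 per arm, emphasis chosen after the fact among many scores and two sets could easily drive the conclusion.

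The per-protocol set adds a separate difficulty. It selects women on attendance after randomisation, at least 16 exercise sessions in one arm and at least 8 education sessions in the other. Women who complete each programme need not be comparable, so this set should not carry a superiority claim.

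**Working it through.** The plan gives no familywise error rate or power to reproduce. Its only input here is the 0.05 level. Sidedness is not stated, so two-sided is assumed.

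**1. Count of scores**, from the outcome assessment sections:

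- Piper: 4 dimensions + total = 5
- QLQ-C30: 1 global + 5 functional + 3 multi-item symptom + 6 single-item symptom = 15
- QLQ-BR23: 5 multi-item + 3 single items = 8
- CES-D 1, State-Trait Anxiety Inventory 2, Godin-Shepard 1, FACT-Cognitive Function 4, sit-to-stand 1

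Total: 5 + 15 + 8 + 1 + 2 + 1 + 4 + 1 = 37. The planned subgroup analyses are not counted. That all 37 are tested is inferred from the scores described and the blanket error level.

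**2. Any of 37 scores, one analysis set, no effect on any score.**

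Expected number of significant results: 37 × 0.05 = 1.85.

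Under independence:

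- Either direction: 1 − 0.95^37 = 0.85
- Favouring MTHE only (0.025 per score): 1 − 0.975^37 = 0.61

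With equal pairwise correlation r, the chance is found by integrating over a shared normal factor:

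| r | either direction | favouring MTHE |
|---|---|---|
| 0 | 85% | 61% |
| 0.3 | 72% | 39% |
| 0.5 | 55% | 28% |

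The two-sided figure falls below 50% at r of about 0.56. The figure favouring MTHE does so between r = 0.1 and r = 0.2.

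**3. Adding the per-protocol set.** Per-protocol women are a subset of the intention-to-treat women, so the two tests of a score are strongly correlated and the error does not double. For one score tested in both sets, 5% becomes about 6.5-8% (per-protocol share 90% down to 60%). For 37 scores at a 75% share, the chance of a result favouring MTHE in either set is about 75%, 49% and 36% at r = 0, 0.3 and 0.5.

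**4. The fatigue conclusion alone.** Four dimensions plus their mean, with dimension correlation from 0.8 to 0.5 and a per-protocol share of 75%:

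| | one set | both sets |
|---|---|---|
| either direction (nominal 5%) | 11-16% | 16-22% |
| favouring MTHE (nominal 2.5%) | 6-8% | 8-11% |

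**5. After the change.** With one score, one set and one test deciding at 0.05, the error of the deciding claim is 5%.

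**The case against.** The strongest reply is that the article names one primary outcome and labels the rest secondary or other. It defines a Piper total and mentions intention-to-treat first, so a reader could guess the deciding test. A condensed article may also leave the deciding score, the analysis set and the multiplicity rule to a fuller document. Unadjusted secondary outcomes are common in a trial of this size.

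Part of this stands. The article is silent on which set decides; it does not give the two sets equal standing. Formal adjustment of the secondary scales would be a preference, not a correction. What remains does not depend on an unseen document: the article itself states a superiority hypothesis covering secondary outcomes, and one error level for all analyses in both sets.

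A reader might infer that a false superiority claim is more likely than not. The documents do not support that:

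- The 85%, 72% and 55% figures count results in either direction, including those favouring health education alone, and assume no effect on any of 37 scores. That is a strong condition for physical activity and sit-to-stand in an exercise trial.
- In the direction of the claim, one set gives 39% at r = 0.3 and 28% at r = 0.5.
- The ambiguity among five fatigue scores brings the primary conclusion nowhere near 50%.

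The Bonferroni post hoc would lower the rates if it alone decided. With six pairwise contrasts at 0.05/6 each, 37 independent scores in one set give 1 − (1 − 0.05/6)^37 = 27%. The article does not say that it alone decides.

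**Conclusion.** The point holds as a defect in what the article states, at moderate size. For the fatigue conclusion, the freedom to choose among five scores and two sets raises the two-sided error from 5% to about 16-22%, roughly three to four times nominal. For the wider hypothesis, at least one significant result somewhere is likely when nothing works (55-85% in one set, for correlations from 0.5 to 0), and at least one falsely favouring MTHE has a chance of about 28-61%.

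These figures rest on no effect on any score tested, on all 37 scores being tested, on assumed correlations and, for both sets together, on an assumed 75% per-protocol share. The documents give neither the correlations nor the share. The defect itself does not rest on them: the hypothesis is broader than any single test, and the text does not say which test settles it.

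**What to change.** - In Statistical considerations, state that superiority is judged on one test only: the between-group comparison of the Piper total score post-intervention, by intention-to-treat, at two-sided 0.05.
- Label the per-protocol analysis a sensitivity analysis, because it selects on attendance after randomisation.
- Report the four Piper dimensions and all secondary scales as supportive, with estimates and 95% intervals and no superiority claim.
- Limit the superiority hypothesis in the Abstract and at the end of the Background to the primary outcome.

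This changes wording only; design, sample size and data collection stay as they are. The cost is that the sponsor gives up unadjusted superiority claims on the secondary scales.
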